## Abstract

**Introduction:**

No evaluated therapeutic approaches, that can efficiently be established in routine mental healthcare, are currently available for traumatised adolescent refugees in Germany. This study evaluates the efficacy of the Stress-Traumasymptoms-Arousal-Regulation-Treatment (START) programme to reduce trauma-related symptoms and psychological distress in traumatised adolescent refugees based in Germany.

**Methods and analysis:**

This randomised, waiting-list-controlled, multicentre trial with a 12-week follow-up will include 174 refugee minors with partial or full post-traumatic stress disorder who are fluent in either Arabic, Dari, English, German or Somali. Eligible refugee minors will be randomised to the START or waiting-list control groups. The manualised 8-week START programme is based on techniques of dialectical behaviour therapy (DBT), fosters adaptive coping with emotional distress and traumatic symptoms and comprises eight therapy modules and a booster session. Study assessments are planned at baseline, post-treatment (ie, after programme participation or waiting time), booster session at week 12 or 12-week waiting time, and at the 12-week follow-up. Primary and coprimary outcomes are changes in psychological distress and traumatic symptoms at post-treatment and will be analysed as response variables in linear mixed regression models. Secondary outcomes are changes in further trauma-related and other psychopathological symptoms, emotion regulation and intermediate effects of the programme at follow-up. We will also assess effects of the programme with ecological momentary assessments and on neuroendocrine stress parameters using hair cortisol.

**Ethics and dissemination:**

This study has been approved by the lead ethics committee of Rhineland-Palatinate and the ethics committees of participating sites. The study results will be disseminated through peer-reviewed publications and scientific conferences.

**Trial registration number:**

DRKS00020771.

Strengths and limitations of this studyRandomised waiting-list controlled multicentre trial with follow-up.Manualised DBT-based psychotherapeutic programme with patient material available in Arabic, Dari, English, German and Somali.Multimodal assessment approach of intervention effects on symptoms, functioning and daily living outcomes by psychometric evaluations, electronic ambulatory assessments (e-diaries) and neuroendocrine stress parameters.Restriction of study participation to refugee minors with language skills in Arabic, Dari, English, German and Somali.

## Background and rationale

Among the forcibly displaced persons worldwide there is a high number of children and adolescents under the age of 18 years.^1^ At the peak of the refugee influx in Germany in 2016, 261 386 of the 745 545 asylum applications recorded in total were filed from refugees under the age of 18 of which 49 786 applications were filed from unaccompanied refugee minors in the care of youth welfare services and without the company of parents or persons with the right of custody. The high percentage of asylum applications filed by refugee minors has remained stable since then though due to political changes the total number of refugees entering Germany has steadily decreased.^2 3^ Of all refugees, children and adolescents, and especially unaccompanied refugee minors, are the most vulnerable group. They are at particular risk of traumatisation before, during and after their flight as well as for mental health problems.^4–6^ Children and adolescents seeking asylum in Germany report an average of eight potentially traumatic experiences, with 98% of unaccompanied refugee minors reporting traumatic events.^5–7^ They are exposed to stress due to insecure legal status and adaptation to new environments, cultural demands and language, the loss of stability provided by their cultural background of origin as well as provided by their families and caregivers if unaccompanied.^8^ In addition to their often prevalent traumatisation, they are also confronted with age-related developmental tasks like peer group integration, identity formation, education, professional training and finding their role in the host society. Cross-sectional studies and reviews assessing mental health problems in refugee minors report prevalence rates of 17%–71% for post-traumatic stress disorder (PTSD), 12%–44% for depressive disorders, 18%–38% for anxiety disorders and 33%–72% for behaviour problems.^9 10^ Longitudinal studies suggest a high risk of chronic mental health problems and indicate that baseline symptom severity, sex, being unaccompanied and post-migration factors like asylum status and access to mental healthcare are predictors of future mental health status.^6 11^ Studies evaluating trauma-related therapy programmes in refugee minors have mostly reported significant effects on trauma and/or additional mental health symptoms. However, conclusive interpretation of the findings is limited by heterogeneous therapy approaches, lack of manualised programmes and methodological shortcomings like lack of power analyses, randomisation and control groups, small sample sizes or heterogeneous study settings such as clinical, school or community settings in high-income countries, but also refugee camps in war regions.^12–17^ Evidence from rigorous methodological approaches like randomised controlled trials (RCTs) is needed to cross-validate the available results in terms of validity, reliability, and generalisability of the programmes.

## Study objectives

The manualised Stress-Traumasymptoms-Arousal-Regulation-Treatment (START) programme was developed from clinical work with traumatised unaccompanied refugee minors in Germany to promote coping with traumatic distress and emotional irritability.^18–20^ An uncontrolled pilot study in 22 traumatised refugee minors showed positive effects on emotion regulation, adaptive strategies, self-control, distress and good feasibility.^18^ A subsequent study confirmed the positive effects on adaptive emotion regulation strategies.^21^

The primary aim of this RCT is to evaluate the efficacy of the START programme in reducing psychological distress and trauma symptoms in traumatised adolescent refugees compared with a waiting-list control group (WL). Main secondary aims are to assess whether treatment effects will remain stable for at least 12 weeks after programme termination (follow-up at week 24) and to assess whether the participants of the START groups improve emotion regulation strategies and mental health compared with WL. As stress and emotions are context-dependent and highly dynamic,^22^ intervention effects are assessed by psychometric instruments and with electronic ambulatory assessment (e-diaries). Ambulatory assessment aims to reduce retrospective biases while gathering ecologically valid data from everyday life near real-time. It has been shown as superior to retrospective psychometric assessment in terms of predicting symptom and treatment outcome^23–26^ and assessing reliably everyday functioning.^27^ We also evaluate intervention effects on the neuroendocrine stress system by assessing hair cortisol, which reflects the cumulative cortisol release over the past months and has been shown to capture treatment effects in PTSD.^28^

The study is part of the START research consortium, which evaluates distress-reducing psychotherapeutic group and preventive family interventions in traumatised toddler, adolescent and young adult refugees and aims to contribute to improved evidence-based therapeutic interventions for refugees within a stepped mental healthcare approach. The consortium comprises the START Adolescent Study, the START Childcare Study,^29^ the START Young Adults Study, and the smartphone-based experience sampling study tracking symptoms and daily living functioning with the use of e-diaries across the START Adolescents and Childcare studies. For further information regarding the consortium, please see wwwmentalhealth4refugeesde. The presented paper reports on the START Adolescents protocol (V.4.0, 16 March 2020) and has been conceived according to the Standard Protocol Items: Recommendations for Interventional Trials (SPIRIT) guidelines.^30 31^ Please also refer to SPIRIT checklist (online supplemental file 1) and to table 1.

10.1136/bmjopen-2021-057968.supp1Supplementary data

**Table 1 T1:** SPIRIT flow diagram

	Study period				
**Time point**	Screening	T0 Study visit Baseline 1 week after random. (WL) or before START Programme	T1 Study visit 8 weeks after T0 (WL) or after START Programme	T2 Study visit 4 weeks after T1 (WL) or at booster session (START)	T3 Study visit Follow-up 12 weeks after T2
**Enrolment**					
Eligibility screen	**X**				
Informed consent	**X**				
Randomisation	**X**				
**Assessments**					
Demographic data	**X**				
Medical history	**X**				
Medication/ psychotherapy	**X**	**X**	**X**	**X**	**X**
Saliva drug screening	**X**				
TONI-4	**X**				
ETI-CA	**X**		**X**	**X**	**X**
K-SADS-PL	**X**				
CGI-S	**X**		**X**	**X**	**X**
C-SSRS	**X**		**X**	**X**	**X**
REB		Weekly			
AUDIT	**X**				
Endangerm. to others	**X**		**X**	**X**	**X**
PSS-10	**X**	**X**	**X**	**X**	**X**
IES-R	**X**	**X**	**X**	**X**	**X**
SDQ self		**X**	**X**	**X**	**X**
SDQ caregiver	**X**		**X**	**X**	**X**
BDI-II		**X**	**X**	**X**	**X**
DERS18		**X**	**X**	**X**	**X**
cPTCI		**X**	**X**	**X**	**X**
CATS-2		**X**	**X**	**X**	**X**
DDNSI		**X**	**X**	**X**	**X**
PMLD		**X**			
Therapy expectation		**X**			
E-Diaries		**X**	**X**	**X**	**X**
Hair cortisol		**X**		**X**	**X**
AE assessments		**X**	**X**	**X**	**X**
**Intervention**					
START programme					
Booster session		[figure not shown]			

AEs, adverse events; AUDIT, Alcohol Use Disorders Identification Test; BDI-II, Beck Depression Inventory, second edition; CATS-2, Child and Adolescent Trauma Screen-2; CGI-S, Clinical Global Impression Scale, severity of illness subscale; cPTCI, Post-traumatic Cognitions Inventory-child version; C-SSRS, Columbia-Suicide Severity Rating Scale; DDNSI, Disturbing Dream and Nightmare Severity Index; DERS-18, Difficulties in Emotion Regulation Scale, 18-Item; ETI-CA, Essen Trauma Inventory for Children and Adolescents; IES-R, Impact of Event Scale-Revised; K-SADS-PL, Kiddie-Schedule for Affective Disorders and Schizophrenia for School-Age Children-Present and Lifetime; PMLD, Post-Migration Living Difficulties Questionnaire; PSS-10, Perceived Stress Scale, 10-Item; SDQ, Strengths and Difficulties Questionnaire; SPIRIT, Standard Protocol Items: Recommendations for Interventional Trials; START, Stress-Traumasymptoms-Arousal-Regulation-Treatment; TONI 4, Test of Nonverbal Intelligence, Fourth Edition; WL, waiting-list.

### Methods and analysis

### Patient and public involvement

The original START programme was developed from clinical work with highly traumatised unaccompanied refugee minors of different countries of origin, who had recently arrived in Germany.^18–20^ The adapted and extended version of the programme, that is evaluated in this RCT, was redesigned according to the participants’ feedback of the pilot study groups, who were also traumatised refugee minors from different countries of origin. The public was not involved when designing the study.

### Trial design and setting

The study is conducted as a 12 weeks, two-arm, randomised, WL-controlled, multicentre trial with a 12-week follow-up and six participating outpatient departments in Germany, all of which are experienced in treating traumatised adolescent refugees. The study is coordinated by the Department of Child and Adolescent Psychiatry and Psychotherapy, University Medical Center, Johannes Gutenberg University, Mainz, Germany. The study intervention comprises an adapted version of the START programme.^18–20^ Languages used in the study for the intervention and the assessments are Arabic, Dari, English, German or Somali. Interpreters are involved if needed. The study is not blinded for the treatment condition, which will be evident to participants, caregivers and study therapists. Recruitment started 1 October 2020. We expect that the last participants will complete the study end of October 2022. Data base lock and analysis of primary outcomes are planned until end of December 2022.

Key stopping rules for patients are a withdrawal of informed consent, unwillingness to further participate in the trial, any factors affecting the patient’s or others’ well-being, for example, acute suicidality or acute endangerment to others, onset of other acute severe mental disorders, alcohol or substance abuse, inpatient treatment of over 2 days, start of concurrent psychotherapy and more than two psychotherapeutic crisis interventions. Key stopping rules for participating centres are non-adherence with the International Council for Harmonisation of Technical Requirements for Pharmaceuticals for Human Use: Guidelines for Good Clinical Practice (ICH-GCP)^32^ or the study protocol, insufficient recruitment of participants, or insufficient data quality. The key stopping rule of the trial is a change in the overall risk-benefit ratio.

## Participants

We will allocate 174 participants to the trial and expect that we will have to screen 240 adolescent refugees for eligibility. Inclusion criteria are: informed consent by adolescents and caregivers, flight background, age between 13.00 and 17.11 years, verbal communication skills and reading comprehension in one of the study languages, non-verbal IQ ≥70, partial or full PTSD, PTSD symptoms are the clinically most impairing condition with at least moderate clinical symptom severity. We kept the exclusion criteria to a minimum, to foster the applicability of the programme in routine care as much as possible. Exclusion criteria are: current substance use disorder and/or harmful alcohol abuse, primary severe mental disorders other than PTSD, acute suicidality or danger to others, unstable psychotropic medication (change of psychotropic medication within the last 2 weeks before baseline assessment), current ongoing psychotherapy, inpatient status or study participation in another clinical trial, unaccompanied refugee minor without a legal representative, known pregnancy. Participants, who attend all assessment visits, will be given a study compensation. Participants will be insured by a clinical trial insurance during the time of study participation. Please see for detailed information about the assessment of eligibility criteria also the sections ‘screening’ and ‘psychometric instruments’. The participants’ study flow is provided in figure 1.

**Figure 1 F1:**
[figure not shown]
Participants‘ study flow. START, Stress-Traumasymptoms-Arousal-Regulation-Treatment.

## Study conduct

### Recruitment

For recruitment, study information is provided to schools, child and adolescent psychotherapists/psychiatrists, social workers, youth welfare providers, at conferences, professional working group meetings, in newspaper articles or interviews, on the institutions’ homepages and on social media. All participants’ information about the study is provided in a caregiver and adolescents’ version in all study languages.

### Trial flow

For a summary of trial flow and assessment visits please see the SPIRIT flow diagram, table 1. All assessments are provided by trained study staff and are performed at the screening visit, baseline (T0), post-treatment (after 8-week START programme or 8-week waiting time; T1), after the booster session or 12-week waiting time (T2), and after 24 weeks at the 12-week follow-up (T3). The maximum time allowed between T0 and T3 is 26 weeks. After termination of the study, all participants are informed about their current diagnostic status and available interventions provided by child and adolescent psychiatric and psychotherapeutic routine care. Participants of the WL are given the opportunity to take part in independent START groups.

#### Screening visit

Assessment of informed consent for study participation, inclusion and exclusion criteria, demographic and medical data. Inclusion of eligible participants, randomisation to the intervention (START) or WL using a web-based randomisation system with permuted blocks stratified by centre (http://randomizer.at).

#### Baseline (T0), post-treatment (T1), booster session (T2), 12-week follow-up (T3) assessments

T0 takes place between one and 2 weeks after randomisation (WL) or before the first programme session (START), T1 within 1 week after the 8-week programme (START) or within 8–9 weeks after T0 (WL), T2 within 1 week after the booster session (START) or 4–5 weeks after T1 (WL) and T3 follow-up visits within 12 weeks after T2 (START/WL). At T0 only, the Post-Migration Living Difficulties Questionnaire (PMLD) and Questionnaire on Therapy Expectation are assessed. At the T0(T1)–T3 visits primary endpoints, trauma symptoms, emotion regulation, general psychopathology, overall clinical severity of mental disorders, suicidality and endangerment to others are assessed and 1 week e-diaries are applied. Hair cortisol is assessed at T0, T2 and T3. Adverse events are assessed at T0–T3 visits and weekly until T1.

### Intervention

Details of the START Adolescents programme are provided in table 2. START Adolescents study groups comprise three to eight participants and are restricted to study participants, who have been randomised to the intervention group. The manualised START group programme is based on DBT-techniques with emphasis on coping with emotional distress and traumatic symptoms, resilience, adaptive functioning and self-efficacy, but not on confrontation with traumatic memories. The group therapy is provided by two therapists through twice-weekly 60 min sessions and interactions are based on validation and acceptance techniques. Written participant programme materials are available in all study languages and if necessary, translators will attend the group therapies.

**Table 2 T2:** Start adolescents programme, modules 1–8 and booster session

Before beginning of START: Written patient information. Handout. Every session: Mindfulness practice and stress signal light. Discussing between-session skills practice. Written patient material. Between the sessions: Participants are asked to train skills and techniques.		
	**Key interventions**	**Practice/training techniques**
**Module 1** Week 1 Sessions 1 and 2	Welcome. Introduction to START. Introduction of participants. Psychoeducation. Explanation of the concepts stress, high stress and stress-regulation skills. Teaching techniques. Skills for reducing distress and high distress. Relaxation techniques.	High-stress skills. Progressive muscle relaxation.
**Module 2** Week 2 Sessions 3 and 4	Consolidation: Available skills. Teaching techniques. Stress signal light for stress/inner tension monitoring and awareness. Emotion regulation strategies: mindful senses (hearing, feeling, tasting, watching, smelling). Skills box.	Mindful sensual experiences. Individual stress signal lights. Individual stimuli for distress/euthymia. High-stress skills. Individual skills boxes.
**Module 3** Week 3 Sessions 5 and 6	Consolidation. Individual skills boxes. Teaching techniques. Skills chains. Individual red light. Self-empowerment/resilience.	Skills chains Self-empowerment
**Module 4** Week 4 Sessions 7 and 8	Consolidation. Available skills. Psychoeducation. Explanation of the concept of crisis and management of crisis. Teaching techniques. Managing crisis: acceptance/skills/safe place. Managing flashbacks. Safety and emergency card. How to recognise change. How to change the moment?	Recognition and managing of crisis. Individual safe place. Skills that change the moment.
**Module 5** Week 5 Sessions 9 and 10	Consolidation. Available skills. Psychoeducation. Sleep disturbances and nightmares. Teaching techniques. Managing nightmares.	Telling/writing nightmares. Skills for managing nightmares.
**Module 6** Week 6 Sessions 11 and 12	Consolidation. Available skills. Psychoeducation. Emotions and emotion awareness. Teaching techniques. Emotion surfing ‘Letting go of emotional suffering’.	Recognising and naming emotions (emotion cards). Individual pleasant and unpleasant emotions. Emotion surfing.
**Module 7** Week 7 Sessions 13 and 14	Consolidation. Available skills, emotion recognition and understanding. Psychoeducation. Emotional network: Interdependence of emotions, thinking, behaviour and prompting stimuli. Skills for emotion regulation.	Role-play/competition: Recognising emotions and thoughts. Understand, name and regulate emotions and related behaviour and thoughts.
**Module 8** Week 8 Sessions 15 and 16	Review and consolidation: Available skills, current difficulties. Crisis plan. Close-out. Farewell celebration. Awarding the participants. Certificates: ‘You did your very best.’ Outlook to booster session.	Experiencing acquired/activated resources (balloon game). Discussing individual skills lists, open needs. Discussing crisis plan/designing emergency cards.
**Booster Session** Week 12 Session 17	Review and consolidation: Helpful skills, difficulties with skills practice within the last 4 weeks, current open needs. Small symbolic gift, for example, little gemstone.	Outlook for future/participants’ wishes/practicing how ‘to turn the tide’.

START, Stress-Traumasymptoms-Arousal-Regulation-Treatment.

The original START Adolescents programme comprised five modules with psychoeducation on trauma, stress, distressing emotions and crises, mindfulness training, arousal regulation, stress reduction techniques, and handling nightmares. For the current study, the START manual^18–20^ was extended by the three additional modules 6–8 and a booster session. The additional modules provide an intensified training of stress reduction skills, mindfulness techniques and additional psychoeducation about emotions and interpersonal effectiveness. Each session follows a defined structure and comprises, as fixed repeated elements, mindfulness training, monitoring one’s own inner tension/stress (‘stress signal light’), reviewing experiences when applying the programme skills, new contents/psychoeducation and skills training. The final session in module 8 is dedicated to a farewell ceremony and to validating and rewarding the participants' efforts and achievements. During the booster session, which is scheduled 4 weeks after programme termination, participants review their experiences when applying the acquired skills and techniques, their open needs, and provide an outlook on their personal future wishes and goals. If standardised risk assessments or participants’ personal information reveal acute danger to the self or others, additional psychotherapeutic crisis interventions will be offered to the participant. Participants with ongoing acute suicidal tendencies or ongoing danger to others after two subsequent crisis interventions must be excluded from study participation and transferred to specific intense psychiatric care.

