## Statistics

### Sample size calculation

The sample size calculation is based on the coprimary outcomes of emotional distress (PSS-10) and traumatic symptoms (IES-R) at T1. Based on available studies^69 70^ we assume in our study an effect size of *d*=0.63 for the PSS-10 and of *d*=0.56 for the IES-R score at T1. This results in a required sample size of n=84 (PSS-10) and n=104 (IES-R) for a one-sided test at an *α*=0.025 level with a power of 80% to detect such differences. The START pilot trial showed a drop-out rate <10% and was conducted as a one-centre single-arm naturalistic trial with mostly inpatients.^20^ We, therefore, calculated the sample size on the assumption of 40% drop-outs between T0 and T1 to account for the multicentre, WL-controlled approach and unstable living conditions of the included population. This amounts to n=174 participants who need to be randomised in our trial.

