### Analysis population and analysis

All randomised participants will be included in the full-analysis set as allocated. All randomised participants, who finish the study according to the study protocol until T2 as planned with no missing values for T1 (primary endpoint) will be included in the per-protocol set for analysis as allocated. All randomised participants will be included in the safety population according to the applied intervention.

Baseline characteristics will be analysed descriptively for the safety, full-analysis, and per-protocol set in the intervention and control group. The primary and coprimary endpoints will be analysed in the full-analysis set. Missing values will be imputed. Endpoints will be assessed as response variables in linear mixed regression models with site and psychotherapeutic group as random effects, intervention group, sex and region of origin as fixed effects, and age, PSS-10 and IES-R baseline scores, respectively, as linear effects with a hierarchical testing procedure that maintains the overall significance level of *α*=0.025. The primary analysis will be repeated in the per-protocol population as a sensitivity analysis. Since the different timing of the T0 baseline examination in the study groups after randomisation could cause biases in the effect estimates, that cannot be estimated or modelled, additional sensitivity analyses will be performed, such as repeating the primary analysis using the screening value instead of the baseline value. Secondary outcomes will be analysed in the full-analysis set. Missing values will not be imputed. The stability of treatment effects up to T3 will be assessed by calculating confidence intervals on the T1–T3 and T2–T3 difference for the PSS-10 and IES-R total scores in the intervention group. Psychometric scales used for assessment of secondary outcomes and hair cortisol concentrations will be analysed according to primary endpoints or descriptively. For the analysis of e-diary data, multilevel models will be used to characterise momentary mechanisms and context-dependent affective experiences, which allow a nested data structure (momentary experiences within participants), and enable different numbers of ratings per participant to be handled quite well.^71^ Safety variables will be analysed in the safety and full-analysis population.

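### Safety and clinical stopping rules do not separate ending treatment from ending assessment, so T1 scores that might still be collected are left to imputation

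*Protocol article*

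**What the plan says.** Under Intervention, the protocol article states: "Participants with ongoing acute suicidal tendencies or ongoing danger to others after two subsequent crisis interventions must be excluded from study participation". The same sentence sends these participants to more intensive psychiatric care. It does not mention T1 or either primary questionnaire.

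Under Trial design and setting, the key stopping rules for patients form a single list. It starts with consent withdrawal and unwillingness to continue. It goes on to acute suicidality or endangerment of others, onset of other acute severe mental disorders, and substance or alcohol abuse. It ends with "inpatient treatment of over 2 days, start of concurrent psychotherapy and more than two psychotherapeutic crisis interventions". The list does not say which of these end treatment only and which also end assessment.

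T1 is a scheduled visit in both arms: "T1 within 1 week after the 8-week programme (START" arm), and 8 to 9 weeks after T0 on the waiting list. Both primary measures, PSS-10 and IES-R, are self-report questionnaires (Primary endpoints).

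Under Analysis population and analysis: "All randomised participants will be included in the full-analysis set as allocated". Then: "The primary and coprimary endpoints will be analysed in the full-analysis set. Missing values will be imputed". The per-protocol set, used for a sensitivity analysis, is limited to randomised participants "who finish the study according to the study protocol until T2 as planned with no missing values for T1 (primary endpoint". The other named sensitivity analysis is "repeating the primary analysis using the screening value instead of the baseline value". The sample size was set "on the assumption of 40% drop-outs between T0 and T1".

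**The concern.** The stopping rules and the analysis set pull in different directions. The analysis follows everyone as randomised, but the stopping rules, read literally, end the participation of those who deteriorate. A participant stopped before T1 then enters the primary analysis with an imputed value, although T1 was already scheduled and consent may still stand.

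The reasons for stopping (persisting acute risk, admission, new psychotherapy, repeated crises) are plausibly related to distress and trauma symptoms, which are the outcomes. Any imputation that predicts T1 from participants who were not stopped may then miss. If stops also differ between arms, the error reaches the treatment effect.

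Such a difference is possible in either direction. START participants meet two therapists twice a week, so risk may be noticed more often in that arm. Waiting-list participants may more often start outside psychotherapy. Both are inferences. The first is weakened because adverse events are assessed weekly until T1 with no restriction to one arm.

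**Working it through.** **Step 1. The plan's own figures.** Inputs from Sample size calculation: d = 0.63 (PSS-10), d = 0.56 (IES-R), one-sided α = 0.025, power 80%, 40% drop-out, 174 randomised. Allocation of 1:1 is assumed.

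- Two-sample t-test, d = 0.56: 51.03, so 52 per arm and 104 in total, as stated.
- Two-sample t-test, d = 0.63: 40.53, so 41 per arm and 82 in total; the article has 84, two more.
- Drop-out: 104 / (1 − 0.40) = 173.3, giving 174 with equal arms, as stated.
- Participants allowed to lack T1, for all causes: 0.40 × 174 = 69.6.

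The point changes none of these figures. The allowance protects power; it does not protect the estimate.

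**Step 2. Following a stopped participant through the text.**

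- Stopped before T1: participation ends (Intervention; Trial design and setting), so read as printed there is no T1 score. The participant stays in the full-analysis set and the value is imputed.
- Stopped at or after T1: the primary endpoint is already collected, so nothing is lost.
- Per-protocol analysis: it requires completion to T2 with T1 present, so it leaves out the same participants.
- Screening-value analysis: it replaces the baseline covariate because T0 is timed differently in the two arms, and has no bearing on a missing T1.

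**Step 3. Illustrative size.** Let a and b be the numbers stopped before T1 in START and on the waiting list. Let k_S and k_W be the true minus the imputed T1 score in each arm, in SD, with higher meaning worse. With 174 / 2 = 87 per arm, and ignoring covariate adjustment:

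shift in (START − waiting list) = (k_W·b − k_S·a) / 87

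With the same k in both arms this is k(b − a) / 87. A negative shift (more stops in START, k > 0) overstates the benefit of START; a positive shift understates it. Equal losses with equal k give 0.

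The documents give neither k nor the numbers stopped, so the values below are assumptions. The 5% imbalance is 0.05 × 87 = 4.35 participants.

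| k (SD) | per net participant, k/87 | % of d = 0.56 | % of d = 0.63 | 5% imbalance, 4.35k/87 | % of d = 0.56 | % of d = 0.63 |
|---|---|---|---|---|---|---|
| 0.5 | 0.006 SD | 1.0 | 0.9 | 0.025 SD | 4.5 | 4.0 |
| 1 | 0.011 SD | 2.1 | 1.8 | 0.050 SD | 8.9 | 7.9 |
| 2 | 0.023 SD | 4.1 | 3.6 | 0.100 SD | 17.9 | 15.9 |

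Shifts are in absolute value; the sign depends on which arm loses more.

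**The case against.** The strongest reply is that this is a safety sentence in a condensed article. It protects minors who remain acutely suicidal or dangerous after two crisis interventions, and whether they should fill in a trauma questionnaire is a clinical judgement. The article lists only key stopping rules and reports on a full protocol (V.4.0) that is not shown and may already provide for T1 after a stop. The imputation method and further missing-data analyses may also be set out elsewhere. The affected group is narrow: acute risk is an exclusion criterion at entry, and the event must persist and end participation within about 8 weeks. Finally, preferring a score taken after transfer to an imputed one is a treatment-policy choice that the article does not state.

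Much of this stands. Transfer to intensive care is right and should stay. The unstated imputation method is not part of this point. The number affected may be very small.

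A reader might infer more than the text supports in two ways. One is that these T1 scores are obtainable: the article does not say so, and some acutely ill participants could not give them. The other is that the safety rule forbids later assessment: it ends study participation but is silent on T1.

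What the reply does not remove is the printed wording. It concerns the study rather than the programme, is mandatory for persisting acute risk, and sits beside a list that treats clinical stops like withdrawal of consent.

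**Conclusion.** The point holds as a cheap improvement, not as a demonstrated bias. Read as printed, safety and clinical stops before T1 produce missing primary scores for a reason plausibly linked to outcome. Those scores are imputed, and neither named sensitivity analysis addresses the loss.

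A reader might go on to conclude that the benefit of START will be overstated. The documents do not support that. They give no stopping rate, no imputation method and no evidence that the true scores would be worse than the imputed ones, and the shift can go either way or cancel. About 0.011 SD per net participant per 1 SD of imputation error is an illustration. It rests on 1:1 allocation, 87 per arm and a simple difference in means.

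**What to change.** 1. **Intervention.** Reword the rule so that persisting acute risk after two crisis interventions ends the START programme or waiting period and leads to transfer to intensive psychiatric care, as now. Add that PSS-10 and IES-R are still sought at T1 where clinically acceptable and consent has not been withdrawn.
2. **Trial design and setting.** After the patient stopping rules, add that, apart from consent withdrawal or unwillingness to take part further, a stop ends the programme or waiting period only, and both questionnaires are still sought at T1 on the same conditions.
3. **Analysis population and analysis.** The model stays as it is. Analyse collected values as allocated, and report stops by reason and arm.

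If the full protocol already provides for this, the published wording only needs aligning with it. Otherwise the change is an amendment needing approval from all ethics committees (Ethics and dissemination), with recruitment already started. The burden on participants is two self-report questionnaires at a visit already scheduled. T1 scores obtained after a stop will also reflect the care that followed, and this should be stated when the effect is interpreted. Sample size is unaffected.
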